#### Analytic Plan

Using the latest version of JMP Statistical Software (currently JMP, version 19.01, SAS Institute Inc, 1989-2025), preliminary analyses will include baseline descriptive statistics and exploratory data analysis. Baseline characteristics of the participants (eg, self-reported MVPA minutes from the screener, demographics, behavior change constructs, anthropometrics, and resting vital signs); recruitment, enrollment, and retention rates; implementation fidelity; adherence and compliance rates; user-burden; acceptability; treatment-specific expectations of benefits and preferences will be summarized in frequency tables for categorical variables and means and SDs for quantitative variables. Qualitative responses to applicable feasibility notifications and open-ended exit surveys will be explored.

Walking behavior and stationary time measures through all 3 periods—baseline, just-in-time, and JITAI—support a 1-way within-subjects ANOVA analysis of continuous measures (eg, average bout duration, speed, distance, and stationary time per study period for each participant) to demonstrate the feasibility of effecting a change in the behavior profile throughout the WWJ study. The intended 1-way within-subjects ANOVA assumes limited outliers, normality, and sphericity, which will be assessed graphically using boxplots, the Shapiro-Wilk test, and Mauchly test, respectively. Outliers, if present, will be assessed for their potential to weaken the analysis and removed if necessary. Nonnormal data will be transformed using the Box-Cox procedure to achieve normality. If sphericity is violated, the Greenhouse-Geisser and Huynh-Feldt corrections will be used. Tukey post hoc testing will be used to explain the differences between WWJ periods. If normality cannot be approximately achieved, the nonparametric Friedman test will be used. The model will be extended to allow for covariates if data screening of other collected demographic measures (eg, education) suggests their importance.

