During implementation, communication drops or a lack of participant adherence may result in missing observations in some instances that inform the planned ANOVA. It will therefore be necessary to explore missing observations as to missing completely at random, missing at random, and missing not at random by using missing data analytics in JMP to associate instances with other study conditions (eg, software considerations and behavioral context). To the extent that the structure leading to the missing observation is not present or identifiable, missing at random or missing completely at random will be assumed for those records, and a linear mixed model will be used, leveraging maximum likelihood for estimation to achieve the within-subjects ANOVA goals without case-wise deletion. Missingness will be summarized in the analysis.

Secondary analyses will examine the initial effectiveness of the walking and stationary prompts. Specifically, the success or failure of notifications to encourage walking (ie, walking faster or longer) or reduce stationary time (ie, registered walking for at least 1 minute). Interarrival times and bouts of walking and stationary times computed at baseline will be summarized in terms of location and spread for continuous values or as frequency tables for bouts of activity.

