### Sample Size and Power Estimates

Power calculations for the planned 1-way ANOVA were performed using G*Power Version 3.1.9.6. [34]. With 3 collapsed times of repeated measures (baseline, just-in-time, and JITAI) and assuming a within-subject correlation of 0.5, given the focus on feasibility for this study, the most effective sample size for predicting our primary outcomes (change in walking behavior and stationary time) was 17 participants with an α level of 0.05, medium-to-large effect size of Cohen f=0.32, and power of 0.8. Allowing for 15% attrition due to dropout or adherence issues, our proposed sample size is 20 participants.

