## Results

Participant recruitment and enrollment began in fall 2022. Data collection was completed in 2024 with a final study sample of 18 participants. Upon completion of the analyses, the results of this study are expected to be submitted for publication. This study was initially funded in March of 2020.

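### The mixed model planned for missing data is to be fitted by maximum likelihood; with 18 participants this understates the within-subject variance by about 5.6% and puts a nominal 5% period test slightly above 5%.

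*Protocol article*

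**What the plan says.** The Analytic Plan section describes two routes to the comparison of the three periods.

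- **Main route.** A one-way within-subjects ANOVA on one average per period per participant. Its assumptions are named: "The intended 1-way within-subjects ANOVA assumes limited outliers, normality, and sphericity". Sphericity is tested with Mauchly's test, and a remedy is given: "If sphericity is violated, the Greenhouse-Geisser and Huynh-Feldt corrections will be used".
- **Missing-data route.** Where no structure behind the missingness can be identified, "missing at random or missing completely at random will be assumed for those records", and then "a linear mixed model will be used, leveraging maximum likelihood for estimation to achieve the within-subjects ANOVA goals". The stated purpose is to avoid dropping incomplete cases.

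For the mixed model the article names the estimator. It does not name a covariance structure, a test statistic or a degrees-of-freedom method. The Results section reports a "final study sample of 18 participants". The Sample Size and Power Estimates section gives three repeated measures, an α of 0.05 and the planning values.

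**The concern.** The ANOVA divides the within-subject sum of squares by (n−1)(k−1). The maximum likelihood random-intercept model, its closest analogue, divides by n(k−1). In a large study the difference vanishes. With 18 people it does not, and it always goes the same way: variance too small, intervals too narrow, p values too low. The replacement model therefore does not quite reproduce the ANOVA it stands in for, and the departure favours a finding of behaviour change.

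A second question follows. The sphericity remedies are attached to the ANOVA. If the mixed model is fitted with a random intercept only, it too assumes equal variances of the period differences, and the article mentions no remedy for that case.

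At stake is whether the stated α of 0.05 holds for the comparisons of walking and stationary behaviour that the sample-size section calls primary, and whether the intervals passed on to a later trial are honest about their precision.

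**Working it through.** **Inputs from the article.** n = 18 (Results); k = 3 periods, α = 0.05, Cohen f = 0.32, within-subject correlation 0.5 (Sample Size and Power Estimates); maximum likelihood (Analytic Plan).

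**The plan's own figure first.** The sample-size section gives "17 participants with an α level of 0.05, medium-to-large effect size of Cohen f=0.32, and power of 0.8". With noncentrality λ = f²·N·k/(1−ρ) and 2 and 2(N−1) degrees of freedom:

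- N = 17: λ = 0.1024 × 17 × 3 / 0.5 = 10.44, power 0.794.
- N = 18: λ = 11.06, power 0.820.

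So 17 reproduces within rounding of the power, and 17/0.85 = 20 gives the planned size.

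**Variance under maximum likelihood (complete data, random intercept).** The divisor is n(k−1) = 36 instead of (n−1)(k−1) = 34. The ratio is 34/36 = 17/18 = 0.944, so the variance is 5.6% too small. Standard errors of period contrasts are too small by a factor √0.944 = 0.972. The F statistic is inflated by 18/17.

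**Exact type I error, random intercept, sphericity true.** The correct statistic follows F(2, 34), with 5% point 3.276.

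| Test used with ML | Threshold on the correct F scale | Actual level |
|---|---|---|
| F, residual df | 3.276 × 17/18 = 3.094 | 5.8% |
| Likelihood ratio | 17 × (exp(5.991/36) − 1) = 3.078 | 5.9% |
| Wald chi-square | (5.991/2) × 17/18 = 2.829 | 7.3% |

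**Exact type I error, unstructured covariance.** Hotelling's T² × 16/34 follows F(2, 16), and maximum likelihood inflates T² by 18/17.

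| Test used with ML | Threshold on the F(2, 16) scale | Actual level |
|---|---|---|
| F with 2 and 17 df | 2 × 3.592 × (17/18) × (16/34) = 3.192 | 6.8% |
| Likelihood ratio | 17 × (exp(5.991/18) − 1) × 16/34 = 3.160 | 7.0% |
| Wald chi-square | 5.991 × (17/18) × (16/34) = 2.663 | 10.0% |

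**Incomplete data (simulation).** Assumption, not in the article: 10% of participant-periods missing completely at random. With 3,000 runs, n = 18, a random intercept and sphericity true, maximum likelihood gives 5.8% (F) and 7.7% (Wald). REML gives 5.0% with F on residual degrees of freedom. The simulation error is about 0.4 percentage points.

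**If the model has a random intercept and sphericity fails.** The epsilon values are assumed. On complete data (200,000 runs), maximum likelihood with F gives 6.3% at epsilon 0.90, 6.9% at 0.80, 7.5% at 0.70 and 9.0% at 0.55. The Greenhouse-Geisser ANOVA stays at 4.5 to 5.0% across the same covariance patterns. REML alone does not cure this: with 10% missing and F it gives 5.4% at epsilon about 0.80 and 8.5% at about 0.55.

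**Cost of an unstructured covariance.** Under sphericity at n = 18, with λ = 11.06, power is 0.820 for F(2, 34) and 0.776 for the Hotelling test on F(2, 16).

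**The case against.** The strongest reply is that the sentence concerns missing data, not the choice between two likelihoods. Maximum likelihood may be generic wording for likelihood-based estimation without case-wise deletion, and so may include REML. If it does, the variance point disappears. The article does not settle this, so at the least the wording needs clarifying; read literally, it names the estimator with the bias.

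A reader might infer that the mixed model discards the ANOVA's sphericity protection. The article does not say so. It names no covariance structure, an unstructured model would need no sphericity assumption, and an article may leave that choice to a full analysis plan. The loss arises only if a random-intercept model is used.

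A reader might also state the error rate as roughly 6 to 10% throughout. That range mixes different models. The 10.0% belongs to an unstructured fit, which does not depend on sphericity at all, and the other high values need a Wald chi-square test or marked non-sphericity. With a random intercept, an F or likelihood-ratio test and sphericity, the excess is under one percentage point.

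Nor does the article show that this model will be the one reported. It says only that missing observations may occur, and lost bouts or days need not empty a two-week average.

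Finally, the pilot's main focus is feasibility, and no efficacy decision turns on 5.8% against 5.0%. That limits the severity. It does not remove the point: every plain maximum likelihood version computed here exceeds 5%, and initial impact is among the article's stated primary aims.

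**Conclusion.** The point holds in a limited form. Read literally, the article fixes an estimator that understates the within-subject variance by about 5.6% at n = 18. The resulting level is 5.8 to 5.9% under the mildest assumptions (random intercept, F or likelihood-ratio test, sphericity true) and about 7 to 10% with a Wald chi-square test or an unstructured maximum likelihood fit. These figures are exact for complete data. The simulation with missing data agrees for the random-intercept F and Wald tests but rests on an assumed 10% missing.

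Further inflation from non-sphericity, for example 6.9% with F at epsilon 0.80, applies only if compound symmetry is assumed, which the article does not state. Severity is minor.

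**What to change.** In the missing-data paragraph of the Analytic Plan, replace maximum likelihood with REML and Kenward-Roger degrees of freedom, and take the period contrasts and their intervals from that model. If REML was always intended, say so.

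This is a one-sentence change, and the article reports the analyses as not yet complete. It still uses all available data without case-wise deletion. Under sphericity it brings the test to about 5%: with complete data and a random intercept, REML restores the ANOVA divisor, and the simulation with 10% missing gave 5.0% using residual degrees of freedom (Kenward-Roger itself was not simulated). The cost is slightly wider intervals.

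It would help to name the covariance structure in the same sentence. An unstructured covariance removes the dependence on sphericity but lowers power at n = 18 from about 0.82 to 0.78 when sphericity holds. Compound symmetry keeps that power but relies on sphericity, even under REML. This is a trade-off for the authors to decide; the correction does not require the unstructured form.

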**Figure 3 figure3:**
[figure not shown]
The WWJ intervention notifications: walk faster, walk longer, and stand up. WWJ: Walking With Just-in-Time Adaptive Intervention.

The learner module (Figure 2) also establishes baseline walking and stationary behaviors during the initial 2-week observation period by passively monitoring behaviors and calculating their applicable averages (eg, average walking speed) per bout. During the just-in-time learning period, intervention notifications are triggered at each instance that participants meet a predetermined threshold for walking and stationary behaviors—unless they have marked themselves as “busy” on their calendar to not burden the user during unsuitable times such as work meetings. The threshold for the walking notifications is set at 250 m from the initial start point of a walking detection. This distance was chosen after trial-and-error field testing among 4 authors ([name], AV, KD, and [name]), which indicated that walking less than 250 m from a given starting location may not align with viable opportunities to walk faster or longer. The WWJ application will send a “walk longer” notification if the system recognizes that the user is in or near a previously tagged location. In all other cases, participants will receive a “walk faster” notification. When stationary behavior is detected for 30 continuous minutes, the application will send the “stand up and move around” notification. The system will determine if these interventions are successful or not (ie, receptiveness) either by comparing the current behaviors in the just-in-time learning period to those in the observation period within the same contexts for walking behavior or by the AW detecting that the user got up and walked around for a minute for stationary behavior. As shown in Figure 2, data collected by the executor during the just-in-time learning period serves as labeled training data to compute and optimize personalized prompting policies for the JITAI period. At the end of the just-in-time learning period, the learner module uses this labeled data to generate a decision-tree–based policy, predicting when and when not to send the intervention notifications to the user based on their current context, past receptiveness, and predicted support needs. As predicting behavior is uncertain, the learning model will deliberately use intervention notifications even if the user may not be receptive, with a 10% chance of such occurrences, to allow behavior change in previously nonoptimal contexts and for the system to learn continually.

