#### WWJ Observation Period, Just-in-Time, and JITAI Periods

For the next six weeks, participants will be instructed to (1) wear the AW on their nondominant wrist during all waking hours, (2) charge the AW during nonwaking hours, (3) tag all locations visited, (4) input and update busy times daily, (5) restart the WWJ app every morning upon waking, and (6) respond to all WWJ app feasibility notifications. During the 2-week observation period, the WWJ app will only monitor walking and stationary behaviors without sending any feasibility or intervention notifications. During the 2-week just-in-time learning period, the WWJ app will (1) monitor walking and SBs, (2) send intervention and feasibility notifications across all appropriate contexts, and (3) assess participant receptiveness to the intervention notifications to begin training for each participant’s unique contexts in which intervention notifications led to successful (vs failed) behavioral changes. During the 2-week JITAI period, the WWJ app will (1) monitor walking and SBs and contextual variables; (2) send notifications at the most opportune moments based on the decision tree policy and the extent to which prior notifications were successful [39]; (3) assess participant receptiveness; and (4) elicit reasons for nonreceptiveness.

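### Notification success is presented as prompt effectiveness, but it counts behaviour that would have occurred unprompted, and no unprompted rate is subtracted

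*Protocol article*

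**What the plan says.** Under Analytic Plan, "Secondary analyses will examine the initial effectiveness of the walking and stationary prompts". The measure follows at once: "the success or failure of notifications to encourage walking (ie, walking faster or longer) or reduce stationary time (ie, registered walking for at least 1", the unit being minutes. The same paragraph describes baseline bouts and interarrival times by location and spread, but does not link them to notification success.

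The scoring rules are under Architecture of the WWJ App and Server:

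- **Stand-up prompt.** "When stationary behavior is detected for 30 continuous minutes, the application will send the “stand up and move around” notification". Success is judged "by the AW detecting that the user got up and walked around for a minute for stationary behavior". No baseline reference enters this rule.
- **Walking prompts.** Success is judged by "comparing the current behaviors in the just-in-time learning period to those in the observation period within the same contexts for walking behavior".

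The sending rule changes between periods. In the just-in-time period, "intervention notifications are triggered at each instance that participants meet a predetermined threshold for walking and stationary behaviors", apart from times marked busy. In the JITAI period, a decision tree trained on those success labels chooses when to send. Prompts still go out in contexts predicted to be unreceptive "with a 10% chance of such occurrences, to allow behavior change in previously nonoptimal contexts and for the system to learn continually".

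In the two-week observation period, "the WWJ app will only monitor walking and stationary behaviors without sending any feasibility or intervention notifications".

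**The concern.** Effectiveness is a difference: what happened after a prompt, minus what would have happened at the same moment without one. The planned measure is only the first term. Someone who has been still for 30 minutes will get up at some point, and if that falls inside the response window the prompt is credited. A walking bout can exceed a personal average through ordinary bout-to-bout variation.

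A second effect comes from selection. The just-in-time period prompts at every threshold crossing. The JITAI period prompts mainly where success was recorded before. If people rise more readily in some contexts than others, the policy moves prompts towards those contexts, and the raw success rate goes up even if prompts change nothing.

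At stake is how the pilot's prompt-level results are read. Strengths and Limitations expects more successful JITAI notifications among participants who give the system more to learn from, and expects the study's effect sizes to inform a later randomised trial. Raw success rates cannot support an inference about learning or a prompt effect size.

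**Working it through.** The article gives no figure for this analysis, so there is none to reproduce. The question is what the planned measure would show if prompts had no effect. The 30-minute trigger, the 1-minute rule, the 10% chance and the final sample of 18 come from the article. All behavioural inputs below are assumptions.

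**1. Stand-up prompt.** Let m be the mean further time a person stays still after 30 minutes, and w the response window. With exponential residual time, null success = 1 − exp(−w/m).

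| m (min) | w = 5 min | w = 30 min | w = 60 min |
|---|---|---|---|
| 15 | 28% | 86% | 98% |
| 30 | 15% | 63% | 86% |
| 60 | 8% | 39% | 63% |

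For example, 1 − exp(−5/60) = 0.08 and 1 − exp(−60/15) = 0.98. A raw rate anywhere in this range is compatible with no effect.

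**2. Walking prompts.** The learner computes observation-period averages per bout, so success is taken to mean exceeding the person's own average.

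- Speed, if symmetric: null success is about 50%.
- Duration or distance, if lognormal with log-SD s: P(bout > mean) = Φ(−s/2). At s = 0.05 this is Φ(−0.025) = 49%; at s = 0.9 it is Φ(−0.45) = 33%.
- With the average estimated from 3 to 10 baseline bouts and s of 0.5 or 1.0, simulated null success for duration is 34% to 45%.

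**3. Selection into the JITAI period.** The simulation had zero prompt effect, 18 participants, 8 contexts each and 10 opportunities per context and period. Spontaneous success varied between contexts. JITAI prompts were sent where just-in-time success was at least 50%, and otherwise with 10% chance.

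| Mean spontaneous success | Between-context SD | Just-in-time | JITAI | Runs with JITAI higher |
|---|---|---|---|---|
| 50% | 0 | 50.0% | 50.0% | 48% |
| 50% | 0.11 | 50.0% | 53.5% | 94% |
| 50% | 0.20 | 50.0% | 60.1% | >99% |
| 50% | 0.29 | 50.0% | 67.3% | >99% |
| 30% | 0.26 | 30.1% | 53.6% | >99% |
| 70% | 0.10 | 70.0% | 71.0% | 70% |

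The gain is nil when contexts do not differ. The largest gain found was 53.6 − 30.1 = 23.5 points. This model fits the stand-up prompt. Walking labels are set against the same context's baseline, which removes most natural differences between contexts. What remains there is sampling error in the context average, which was not modelled.

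**4. Can the observation log supply the missing rate?** Walking and Stationary Behaviors says timestamped bouts are collected once their thresholds are met. At the Background section's paces of 0.82 to 1.8 m/s, a one-minute walk covers 60 × 0.82 = 49 m to 60 × 1.8 = 108 m, well short of 250 m. Short walks may therefore be absent from the log. The duration of stationary bouts is recorded to the second, so the end of a stationary bout is available as a substitute.

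**The case against.** The strongest reply is that the plan already contains an unprompted reference. Walking prompts, two of the three types, are scored against the same person's observation period in the same contexts. A reader might infer from the stand-up rule that no prompt has any comparator, and the text does not support that. The reply stands to that extent. But a reference used as a per-bout threshold still passes a third to a half of unprompted bouts, and nothing subtracts that share.

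Three other strong readings also fail.

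- **That JITAI must automatically beat just-in-time.** The gain disappears when spontaneous success is equal across contexts.
- **That null success is high.** For the stand-up prompt it is unknown.
- **That prompted bouts exceed baseline on distance by construction, because only bouts reaching 250 m are prompted.** Averages are described per bout, but the data-collection text suggests that baseline bouts may also be recorded only once the threshold is reached. The point cannot be settled from the article.

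It is also fair that no test of success rates between periods is planned, that the analysis is secondary in a pilot focused on feasibility, and that a response window or scoring model may sit in a fuller document. Their absence is not the criticism. The article itself names effectiveness as the target and specifies a measure that cannot deliver it.

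**Conclusion.** The point holds for the secondary prompt-level analysis. Stand-up success includes spontaneous rising. Walking success has a null level of roughly one third to one half, given the assumed bout distributions and an own-average cut-off. Raw JITAI success will tend to exceed raw just-in-time success without any prompt effect whenever spontaneous success differs by context, mainly for the stand-up prompt. Across the assumed scenarios that gain ran from 0 to about 24 points. The design presumes that receptiveness differs by context, since the policy exists to exploit it, but the article gives no data on how much spontaneous success varies.

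Raw rates should therefore not be read as effectiveness or compared across periods. The within-subjects ANOVA on bout duration, speed, distance and stationary time includes the unprompted baseline and is not affected.

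**What to change.** Apply the same triggers (30 stationary minutes, 250 m walked, not marked busy) to the observation-period log as virtual prompts. Score them with the identical success rule and response window. If short walks were not logged, use the end of the stationary bout as the stand-up outcome for both real and virtual prompts. Report prompted minus unprompted success within matching contexts, by prompt type, from a logistic mixed model with participant effects. If this is not done, call the raw figures response rates and make no effectiveness or between-period claim.

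The cost is programming on timestamped bouts while analyses are still pending. Intervals will be wider and reported effects smaller than the raw percentages. The contrast remains before-versus-after, so it does not remove time trends.

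An optional supplement, only if withheld decision points were logged (the article does not say they were), is to compare the 10% chance sends with withheld points in contexts classed as unreceptive. Assume 6 stand-up points a day, 14 days, 18 people, half classed unreceptive and 30% success. That gives 6 × 14 × 18 × 0.5 = 756 points, 75.6 sent and 680.4 withheld. The 95% half-width is 1.96 × √(0.21/75.6 + 0.21/680.4) = 0.109, or about 11 points before clustering and 15 with a design effect of 2.
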